## Methods/Design

### Study Design and Objectives

The TRADE-HF is a prospective, open-label, randomized, multi-center, two parallel arm study. The study has been approved by the local Ethic Committees of all 20 participating centers and has been registered to http://www.clinicaltrials.gov site (NCT00345592). Enrollment started in November 2006. The steering committee of the study is responsible for the study design and its amendments.

Primary objective of the TRADE-HF study is to demonstrate a reduction in the combination of hospitalizations for cardiovascular causes or death for cardiovascular causes or development of permanent AF, using a device-based treatment of atrial arrhythmias (i.e. automatic therapy) compared to a traditional approach including hospitalization for symptoms and and/or in-hospital treatment of AT/AF (i.e. traditional therapy). Automatic therapy implies that atrial arrhythmias are detected by the device itself which treats the rhythm automatically within 3 hours after episode onset with a predetermined sequence of programmed electrical therapies (anti-tachycardia pacing and electrical shock). On the other side in the traditional arm automatic shock therapy is not active; therefore, patients who will experience symptomatic atrial arrhythmias at home will refer to their center, where treatment of the atrial arrhythmia will be done according to center's practice (e.g. drugs, external cardioversion, device shock commanded by the physician in a hospital environment). Hospitalizations for cardiovascular causes will include any unplanned cardiac cause hospitalization including day hospital, access to the emergency units and in-hospital procedures of AT/AF cardioversion. Permanent AF is considered as any form of AF that is found to be refractory to drug or electrical therapy, for which the physician resigns to take additional actions to restore sinus rhythm and that persists additionally for at least one month. After obtaining informed consent, a three-month observation period ensues, during which the device parameters are optimized, data on atrial arrhythmias are collected and patient's response to the device treatment is assessed. Thereafter, patients are randomized to the two different treatment arms, automatic and traditional therapy in a 1:1 ratio. After being randomized, patients are followed for three years to assess endpoints. The study flowchart is shown in figure 1.

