### Interventions and Follow Up

After obtaining informed consent, patients' baseline data are collected, including demographic background and medical history. A clinical evaluation performed at the time of enrollment includes NYHA class assessment, an electrocardiogram, an echocardiogram and Qol assessment using the Minnesota-Living With Heart Failure questionnaire. During the three-month observation period before randomization, we collect data on the incidence of supraventricular arrhythmia and clinical events; deaths from any cause or chronic atrial fibrillation before randomization are considered dropouts. Patients are randomized by means of a centralized, computer-generated randomization list, with a 1:1 ratio; given that both patients and physicians are aware of the randomized treatment and that patients are specifically trained to manage their symptoms in two different ways depending on the study arm, patients and investigators are not blinded with respect to treatment. At the randomization visit, NYHA class, QoL and atrial and ventricular function are assessed (the latter by echocardiography) in order to evaluate the response to CRT. After randomization, patients are followed up for a total duration of 3 years, with planned ambulatory visits every 6 months.

At follow-up visits a clinical assessment is performed including NYHA class staging, ECG and medical therapy. QoL assessment and echocardiography are mandatory one and two years after randomization. Data regarding events such as hospitalization are collected over the entire follow-up period.

Device shocks and all interventions performed to treat atrial arrhythmias (drug, electrical or other therapy, repeated or not) are collected for both study arms. A protocol for the management of atrial arrhythmias in the traditional arm has not been predefined, but left to center's specific therapeutic practice and decision making, and may range from simple observation of the response to drugs of the hospitalized patient to repeated attempts of internal cardioversion done with the device in a in-hospital environment. The only requirements for this arm are 1) automatic shock set to "off" and 2) arrhythmia treatment performed at in-hospital environment.

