### Sample Size

Patients treated for CRT in two large randomized clinical trials, the COMPANION [13] and CARE-HF [14] studies, yielded a respective incidence of 62% and 38% in deaths or hospitalizations due to cardiac reasons after a two-year follow-up period. According to the AFFIRM study [22], the evolution to chronic AF may range between 20% and 25% after two years, in patients who are likely to experience recurrent AT/AF. In HF patients, the prevalence of AF is reported to vary from 10% to 50%, with higher values in older patients and in those with superior NYHA class [23]. Additionally, the incidence of new-onset AF in these patients ranges from 3% and 10% per year [23]. A study of a large cohort of heart failure patients has recently revealed that around one third of hospitalized patients had ECG evidence of AF [24]. Based on these data, we assumed that around 35% of patients in both study arms of the TRADE-HF study will have experienced at least one episode of atrial arrhythmia after three years and that around 60% will have experienced at least one hospitalization for cardiac reasons or persistent/chronic AF or death from cardiovascular causes. Patients treated automatically with the device are expected to have a lower rate of events. The effectiveness of treating AT/AF with a dual-defibrillator is very high and reported to be around 90% in different settings [15,16]. Assuming a 60% risk for combined endpoints in the traditional arm versus a 43% risk in the device-managed arm, using a two-tailed alpha of 0.05, with a Cox proportional hazards regression model the study will need a total of 360 patients (180 per group) in order to achieve a power of 90% and demonstrate a difference in primary endpoint rates among patients in the device-managed arm versus those in the traditional arm. Assuming a 15% attrition rate during the study, due to loss to follow-up or failure to adhere to the study design, the total sample size will amount to 414 patients (207 per group).

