### Data Analysis

Descriptive statistics will be presented for the collected variables, overall and according to the randomization group; for categorical variables absolute and relative frequencies; for continuous variables mean, standard deviation, median, 25th-75th percentile, minimum and maximum. Baseline characteristics of the two study arms will be listed. Cox modeling will be used to perform the primary analysis and assess the association between treatment (traditional vs. device-managed) and the primary endpoint. Hazard ratios and their 95% confidence intervals will be presented together with Kaplan-Meier cumulative survival and with event rates (per 100 persons per year) in each group. The model will include the following potential confounders: evidence of AT/AF in the patient's medical history or recorded by the device before randomization and patients' response to CRT at randomization. In particular, group effects will be tested by interaction terms comparing the treatment effect in patients who are or are not responders to CRT at randomization. Competing events (causes of death other than cardiovascular, transplant or ventricular assist device implant) will be censored at the time they occur. The primary analysis will be done according to Intention to treat (ITT) i.e. automatic shocks programmed according to randomization. Survival analysis techniques will be used to evaluate time-to-event for the evolution to chronic AF and for both subgroup analyses (CRT responders and AT/AF). In case the primary endpoint is fulfilled, additional post-hoc analyses will be performed. In particular a positive response to CRT responsiveness will be analyzed with respect to the planned variables by means of a logistic regression model. The device's ability to manage and correctly classify atrial arrhythmia will be evaluated considering the sensitivity, specificity and accuracy of the device's classification compared to that made by the Event Committee. Quality of life scores, number and total duration of hospital admissions (for all causes, cardiac causes and for heart failure), total duration of AF and total costs will be compared between the two study arms after 3 years using the appropriate statistical test, according to distribution. For economic analysis costs are estimated for hospitalization (reasons, entry date, duration, department), interventions and instrumental examinations performed. A P value of at least 0.05 will be used for statistical significance.

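### Total AF duration is compared between arms with no baseline covariate named, although pre-randomization arrhythmia data are already held; adjusting for them is a free gain in precision of uncertain size

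*Protocol article*

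**What the plan says.** The Data Analysis section lists total AF duration with quality of life, hospital admissions and costs, and says that "total duration of AF and total costs will be compared between the two study arms after 3 years using the appropriate statistical test". Distribution is the only stated rule for choosing the test, and no covariate is named.

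The same section puts "evidence of AT/AF in the patient's medical history or recorded by the device before randomization" into the primary Cox model as a covariate.

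Two sections show that arrhythmia is recorded before randomization. Under Study Design and Objectives, in the three-month observation period "data on atrial arrhythmias are collected and patient's response to the device treatment is assessed". Under Interventions and Follow Up, "During the three-month observation period before randomization, we collect data on the incidence of supraventricular arrhythmia and clinical events"; medical history is also taken at enrolment. Study Design and Objectives further plans to relate AF burden in three classes (none, below 10%, above 10%) to CRT response, at randomization and one year later.

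For the three-year horizon, the Sample Size section makes this assumption: "around 35% of patients in both study arms of the TRADE-HF study will have experienced at least one episode of atrial arrhythmia". The article gives no variance, correlation or power for AF duration.

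**The concern.** Patients are enrolled whatever their arrhythmia history, apart from refractory chronic or persistent AF. On the plan's own figure about 65% (100% − 35%) would have no AF in three years, and the rest will probably differ widely. The spread of the outcome then comes mainly from which patients have AF and how much. A pre-randomization measure of the same trait can remove part of that spread, and adjusting for it is legitimate because it precedes allocation.

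The authors treat earlier AT/AF as worth adjusting for in a composite that depends only partly on AF. The case for adjusting AF duration itself is at least as strong. At stake is the precision of the comparison closest to the mechanism argued in the Discussion, that automatic therapy shortens the time to sinus rhythm.

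**Working it through.** **1. The plan's own figure.** For 60% versus 43%, two-sided 0.05 and 90% power, with mean proportion 0.515:

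n per arm = [1.960·√(2·0.515·0.485) + 1.282·√(0.60·0.40 + 0.43·0.57)]² / 0.17² ≈ 180, or 360 in total.

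This reproduces the Sample Size section. It concerns the primary endpoint only; 180 per arm is used below as the available number.

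**2. Gain in the ideal linear case.** If baseline and outcome correlate at ρ (assumed), adjustment leaves a share 1 − ρ² of the variance. Starting from 80% unadjusted power,

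power = Φ[(1.960 + 0.842)/√(1 − ρ²) − 1.960].

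| ρ | variance removed | power |
|---|---|---|
| 0.2 | 4% | 81.6% |
| 0.3 | 9% | 83.6% |
| 0.4 | 16% | 86.4% |
| 0.5 | 25% | 89.9% |
| 0.6 | 36% | 93.8% |
| 0.7 | 49% | 97.5% |

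The gain is 2 to 6 points up to ρ = 0.4 and large only from about 0.5. An outcome with 65% zeros does not follow this formula closely, hence step 3.

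**3. Simulation with run-in burden as the only covariate.** There were 180 patients per arm and 1,500 trials per row. From the article: 35% with any AF at three years. Assumed: 5 to 20% with AF in the run-in, the latent correlation, and treated burden multiplied by 0.3 with the share of patients with AF unchanged. Entries are power (%) without → with the covariate.

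| AF in run-in | latent correlation | observed correlation (log scale) | ranks | log scale |
|---|---|---|---|---|
| 5% | 0.5 | 0.26 | 19.5 → 19.7 | 51.3 → 52.1 |
| 5% | 0.7 | 0.38 | 17.3 → 20.1 | 48.4 → 56.8 |
| 10% | 0.5 | 0.31 | 18.9 → 20.5 | 51.4 → 54.8 |
| 10% | 0.7 | 0.46 | 19.5 → 22.7 | 48.2 → 57.9 |
| 20% | 0.5 | 0.36 | 18.0 → 20.1 | 47.9 → 54.9 |
| 20% | 0.7 | 0.54 | 18.1 → 20.9 | 45.9 → 61.9 |
| 5% | 0.9 | 0.51 | 18.3 → 20.7 | 48.5 → 62.6 |
| 10% | 0.9 | 0.63 | 15.6 → 22.1 | 46.9 → 69.5 |
| 20% | 0.9 | 0.75 | 18.2 → 34.7 | 48.5 → 86.3 |

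At latent correlation 0.5 to 0.7 the gain is 0 to 3 points on ranks and 1 to 16 on the log scale. At 0.9 it is 2 to 17 and 14 to 38. Each power carries a simulation error of about 1 point (√(0.2·0.8/1500) = 1.0%), so the smallest gains cannot be told from zero.

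**4. Run-in burden plus AT/AF evidence.** History can mark likely AF patients even when the run-in is silent. Assumed: AF seen in the run-in in 20 to 40% of AF patients (0.35 × 0.20 = 7% to 0.35 × 0.40 = 14% of all) and latent correlation 0.5 to 0.7. The gain was about 2 to 10 points on ranks (base about 12%) and 9 to 33 on the log scale (base about 52%). Type I error was 5 to 6%. A separate set of runs at latent correlation 0.5, with AT/AF history in 30 to 50% of AF patients and 10 to 20% of the others, gave 2 to 8 points on ranks and 16 to 29 on the log scale.

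**5. How informative might the run-in be?** The Sample Size section cites AF prevalence of 10 to 50% and new onset of 3 to 10% per year. The Discussion cites 25% recurrence within six months among CRT candidates with an AF history. Taking prevalence as history and spreading recurrence evenly, three months give 0.25 × (10 to 50%)/2 = 1.25 to 6.25%. New onset adds (3 to 10%)/4 = 0.75 to 2.5%. The sum, about 2 to 9% of patients, points to the low end of step 3 for run-in burden alone.

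**The case against.** The strongest reply has four parts.

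- **Scope.** This is a journal article, and covariates for a supporting comparison may be fixed in an analysis plan not shown. The text leaves the test open and never calls it unadjusted. That stands as a caution. But a rule of choosing by distribution describes a choice among two-arm tests, and the same section does name covariates for the primary model.
- **Weak baseline.** Most run-in values will be zero. Patients with chronic AF before randomization leave as dropouts, which removes the highest baselines. Device parameters are still being optimized in that period. This stands, and it is why the gain on ranks is small.
- **Importance.** AF duration is absent from the listed secondary objectives, and the Discussion says the study is not powered for the benefit of prompt treatment. This stands and limits the weight of the point.
- **Data.** Interventions and Follow Up speaks of incidence in the run-in, so a run-in duration is likely but not stated. The burden classes planned at randomization suggest that more than incidence is held.

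A reader might also infer that run-in arrhythmia is used nowhere but as a yes/no term in the Cox model. The article does not support that: it also plans an AT/AF subgroup analysis and relates burden classes to CRT response.

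**Conclusion.** The point holds as an optional efficiency improvement to a supporting outcome. The planned comparison is unbiased and keeps its type I error, but is less precise than the data already collected allow. Under the assumptions shown, adjustment is worth about 0 to 10 power points on ranks and roughly 1 to 30 on a log scale (33 in the most favourable setting with both covariates). Only an assumed latent correlation of 0.9 takes run-in burden alone beyond these ranges. A two-part model was not simulated; a gain of the log-scale kind is expected there.

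A reader might infer that the comparison loses much of its power, or that adjustment is worth 19 to 96% more patients (1/(1 − 0.4²) = 1.19; 1/(1 − 0.7²) = 1.96). The article supports neither. It gives no correlation, and that formula belongs to a linear model, not to an outcome that is about 65% zeros. Nor does a chance imbalance in high-burden patients make the unadjusted test invalid; its error rate already covers that.

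**What to change.** State in the analysis plan that total AF duration will be analysed with a model containing arm, AT/AF evidence before randomization (history or device record) and run-in AF burden. Use burden per monitored day if it was recorded. Otherwise use the three burden classes already planned, after assigning a value of exactly 10% to one of them.

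Prefer a log-scale or two-part model with robust standard errors; rank ANCOVA is the alternative. For a two-part model, test both parts jointly, since the positive part alone compares groups formed after randomization. Fix the model before outcome data by arm are seen, and report the unadjusted test as supportive.

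The cost is a few lines of analysis text and a check of what the run-in records contain. No patients or visits are added.

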**Figure 1 F1:**
[figure not shown]
**Study flowchart**. RND: Randomization.

Secondary objectives include: the performance assessment of automatic atrial therapies, and a comparison between the automatic-managed and traditional therapy arm of the following outcomes: in-hospital costs, Quality of Life (QoL) scores, number of hospital admissions and the separate components of the primary endpoint.

An exploratory analysis will be done in order to investigate the response to CRT treatment for the enrolled patients. A positive response to CRT is considered a relative LVEF increase ≥ 20% and/or a relative LVESV decrease ≤ 15% measured at echocardiographic recording associated with a functional assessment defined as reduction of at least one NYHA class or of 15 points at Minnesota living with heart failure score for NYHA class III patients or at least stable NYHA class or 10 points decrease at Minnesota living with heart failure score for NYHA class II patients. This definition reflects patient's cardiac remodeling associated to a functional improvement in highly symptomatic patients or at least a stable functional condition in mild symptomatic patients. The proportion of CRT responders will be analyzed at time of randomization and one year after randomization; additionally a correlation, separately at the two time points, will be searched among the proportion of CRT responders, the burden of atrial fibrillation (total percentage of recorded AT/AF episodes: 0; <10%; >10%) and the target site of left ventricular lead (lateral wall vs. other).

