If a primary endpoint event, other than patient death, occurs, the patient continues to be followed over the entire 2-year period in order to assess secondary endpoints. Crossover may occur at any point during the follow-up: patients may withdraw from the device-controlled therapy arm when atrial shock therapy is disabled due to severe discomfort related to shocks or too frequent atrial shock therapies; patients may cross from the traditional therapy to the device-controlled arm when atrial shock therapy is enabled chiefly because the number of hospital admissions for atrial cardioversion becomes too frequent. Patients who present with permanent/chronic AF, regardless of the randomization arm, start rate control therapy with the device's atrial therapy set to off: this is not considered a crossover, as the patient has already reached the primary endpoint.

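### The planned 3-year quality-of-life comparison gives no role to the randomization score or to the year 1 and year 2 scores, the only post-randomization scores the protocol requires

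*Protocol article*

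**What the plan says.** All references are to the protocol article.

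- **Objective.** Study Design and Objectives lists the secondary outcomes to be compared between arms: "in-hospital costs, Quality of Life (QoL) scores, number of hospital admissions and the separate components of the primary endpoint".
- **Analysis.** Data Analysis groups QoL with admissions, AF duration and costs. It says these "will be compared between the two study arms after 3 years using the appropriate statistical test, according to distribution". No model, covariate or rule for deaths is given for QoL.
- **Scores before treatment starts.** Interventions and Follow Up has the Minnesota questionnaire completed at enrollment ("an echocardiogram and Qol assessment using the Minnesota-Living With Heart Failure questionnaire"). It is repeated after the three-month observation period: "At the randomization visit, NYHA class, QoL and atrial and ventricular function are assessed". The stated purpose of that second score is to evaluate response to CRT.
- **Scores after randomization.** The same section says "QoL assessment and echocardiography are mandatory one and two years after randomization".
- **Length of follow-up.** The same section says "After randomization, patients are followed up for a total duration of 3 years, with planned ambulatory visits every 6 months". For patients who have a non-fatal primary event it then says "the patient continues to be followed over the entire 2-year period in order to assess secondary endpoints".

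**The concern.** Two things do not fit together.

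First, the analysis points to three years, but the collection schedule requires QoL only at one and two years, and one sentence gives two years as the period for secondary endpoints. Read literally, the comparison rests on a score that nothing obliges a site to collect, while the two mandatory scores have no stated part in it. If three years marks only the date of the analysis, the QoL time point is undefined.

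Second, a test picked by the shape of the distribution leaves aside the score taken at randomization, which is likely to be one of the best predictors of later scores. Elsewhere in the same paragraph the authors name a model where they want one: Cox regression with covariates for the primary endpoint and logistic regression for CRT response.

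At stake is the precision and clarity of a secondary outcome that the Background names as a goal of AF treatment and on which the Discussion says the effect is unknown. There is also a question of interpretation. Patients who die have no later score, and cardiovascular death is a component of the primary endpoint, so the set of patients with a score could differ between arms.

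**Working it through.** **The plan's own figures.** None is given for QoL: no SD, target difference, correlation or mortality. The one sample-size figure concerns the primary endpoint. The two-proportion formula reproduces it at 60% v 43%, two-sided alpha 0.05, power 90%: (1.960 × √(2 × 0.515 × 0.485) + 1.282 × √(0.60 × 0.40 + 0.43 × 0.57))² / 0.17² = 179.5, so 180 per arm and 360 in total. It says nothing about QoL. Everything below rests on assumed ranges.

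**Step 1. Time points side by side.**

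| Place | QoL time point or period |
|---|---|
| Interventions and Follow Up, mandatory assessments | 1 and 2 years |
| Interventions and Follow Up, patients with a non-fatal primary event | 2-year period for secondary endpoints |
| Interventions and Follow Up, overall follow-up | 3 years, visits every 6 months |
| Data Analysis, QoL comparison | 3 years |

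The analysis time point matches neither mandatory assessment.

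**Step 2. Precision from the randomization score.** Let r be the correlation between the randomization score and a later score (assumed). At one visit, relative to comparing the later scores alone, adjustment multiplies the variance by 1 − r² and the standard error by √(1 − r²). If the unspecified test were applied to change scores, the change-score variance would be 2(1 − r) times that of the later score. The adjusted variance would then be (1 − r²) / [2(1 − r)] = (1 + r)/2 of the change-score variance.

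| r (assumed) | Variance, adjusted v score alone | SE reduction v score alone | Equivalent gain in patients, 1/(1 − r²) | SE reduction v change score |
|---|---|---|---|---|
| 0.3 | 0.91 | 5% | 10% | 19% |
| 0.5 | 0.75 | 13% | 33% | 13% |
| 0.6 | 0.64 | 20% | 56% | 11% |

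As an illustration, take an assumed true difference of 0.3 SD and an assumed 20% of 180 per arm dead, leaving 144 scored per arm. Power is Φ(0.3 × √(144/2) / √(1 − r²) − 1.96). This gives 72% without adjustment, 76% at r = 0.3 and 84% at r = 0.5.

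**Step 3. How large could survivor bias be?** Assume QoL is normal with SD 1 and unaffected by treatment, and that a patient dies when a risk variable, correlated c with QoL, passes a threshold. With mortality p, the survivors' mean shifts by c × φ(z)/(1 − p), where z is the (1 − p) normal quantile. The factor φ(z)/(1 − p) is 0.274 at 15%, 0.350 at 20% and 0.424 at 25%.

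| Mortality (assumed), traditional v automatic | c = 0.3 | c = 0.5 |
|---|---|---|
| 20% v 20% | 0 SD | 0 SD |
| 20% v 15% | 0.3 × 0.076 = 0.023 SD | 0.5 × 0.076 = 0.038 SD |
| 25% v 15% | 0.3 × 0.149 = 0.045 SD | 0.5 × 0.149 = 0.075 SD |

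Where the bias is not zero, it makes the arm with lower mortality look worse.

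**The case against.** The strongest reply is that this is an article. One sentence covers several secondary outcomes, and it neither excludes baseline adjustment or change scores nor states a rule for deaths. Such detail commonly sits in a full protocol or SAP, which is not shown. That stands as far as it goes: nobody can say from this document that the randomization score will be ignored or that patients who die will be dropped. It does not remove the mismatch of time points, which lies within the article, or the fact that what is written for QoL is a test and not a model.

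A second reply is that in a randomized comparison, omitting the baseline score causes no bias. That is correct, and the gain at r = 0.3 is modest.

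A reader might go further and infer that the trial plans a biased survivors-only comparison that could hide or reverse a benefit. The documents do not support this:

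- They give no mortality by arm, and with equal mortality the bias is nil.
- A 10-point mortality difference is demanding. The Sample Size section expects about 35% of patients to have an atrial arrhythmia in three years. If the benefit came only through them, it would have to be about 10/0.35 = 29 points in that group.
- The Discussion itself cites a large randomized trial in which rhythm control did not reduce cardiovascular death.

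A reader might also combine the attrition allowance with an assumed mortality of 10% to 25% and conclude that only 64% to 77% of patients would have a score (0.85 × 0.75 to 0.85 × 0.90). But the allowance reads "Assuming a 15% attrition rate during the study, due to loss to follow-up or failure to adhere to the study design". It includes non-adherent patients, who can still complete a questionnaire, so this is a worst case.

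Finally, a repeated-measures model does not itself remove truncation by death: it treats later scores as missing. That also stands, and is why a separate analysis is needed for deaths.

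**Conclusion.** The point holds as one of precision and of an unreconciled time point. The stated QoL comparison is set at three years, where no score is required, and it gives no role to the randomization score or to the mandatory scores at one and two years. Under assumed correlations of 0.3 to 0.6, adjustment lowers the standard error by about 5% to 20%. The direction of that gain does not depend on mortality.

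The survivor question is a reason to report deaths and missing scores openly, not a demonstrated bias. Its possible size is 0 SD with equal mortality and roughly 0.02 to 0.08 SD under assumed differences of 5 to 10 points and death-QoL correlations of 0.3 to 0.5. QoL is a secondary outcome, and the primary conclusion is untouched.

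**What to change.** 1. For QoL, replace the distribution-based test with a repeated-measures model of the post-randomization Minnesota scores, with terms for arm, visit and their interaction, adjusted for the randomization score. It uses every patient with at least one follow-up score.
2. Reconcile the QoL time point across Interventions and Follow Up (mandatory at years 1 and 2; 2-year period for secondary endpoints) and Data Analysis (3 years), and name the visit at which the arms are contrasted.
3. Report the number of deaths and of missing scores by arm and visit beside the QoL result.
4. Add a supportive rank-based comparison in which death is the worst outcome.

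The cost is revised wording and slightly more programming. The model can be fitted to scores already mandatory, so no new data are needed. The downside is that the rank result mixes death with QoL, so it should be read beside the model estimate and not in place of it.

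### The significance rule in Data Analysis is worded in the wrong direction and contradicts the two-tailed alpha of 0.05 used to size the trial

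*Protocol article*

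**What the plan says.** Three statements in the protocol article bear on the threshold for significance.

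- **Data Analysis, last sentence:** "A P value of at least 0.05 will be used for statistical significance". It is not tied to a particular test. By its position it covers the primary Cox analysis, the interaction with response to CRT, the subgroup analyses, and the comparisons of quality of life, admissions, AF duration and costs.
- **Sample Size:** the number of patients was calculated "using a two-tailed alpha of 0.05", for 90% power on the primary endpoint.
- **Data Analysis, on the Cox model:** "Hazard ratios and their 95% confidence intervals will be presented".

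No other sentence in the article states the direction of the rule.

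**The concern.** A P value of *at least* 0.05 is one that is 0.05 or larger, which is the region in which a two-sided test at alpha 0.05 does not reject. The analysis section therefore states the complement of the rule on which the trial was sized.

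A pre-specified rule exists so that a later reader can check the reported conclusions against it without having to guess. Here the reader must assume the opposite of what is written. For the primary comparison, the Sample Size section shows what was meant. For the interaction test and the secondary comparisons, the last sentence of Data Analysis is the only significance rule stated.

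**Working it through.** **Inputs from the protocol article**

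- Event risks (Sample Size): "Assuming a 60% risk for combined endpoints in the traditional arm versus a 43% risk in the device-managed arm".
- Alpha 0.05, two-tailed; power 90%; 360 patients, 180 per group (Sample Size).
- Allocation 1:1 and three years of follow-up after randomization (Study Design and Objectives).

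**Step 1. Reproduce the plan's own figure.** For two proportions with pooled variance and no continuity correction:

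n per arm = [z(0.975)·√(2·p̄·(1 − p̄)) + z(0.90)·√(p₁(1 − p₁) + p₂(1 − p₂))]² / (p₁ − p₂)²

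With p₁ = 0.60, p₂ = 0.43 and p̄ = 0.515:

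- first term: 1.960 × √0.49955 = 1.385
- second term: 1.2816 × √0.4851 = 0.893
- n = (1.385 + 0.893)² / 0.17² = 5.189 / 0.0289 = 179.5, rounded up to 180 per arm, or **360 in total**

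This equals the stated figure. Other formulas, for comparison:

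| Method | Total N |
|---|---|
| Two proportions, two-sided | 360 |
| Freedman, two-sided: HR = ln 0.57 / ln 0.40 = 0.613; 184 events / 0.515 | 358 |
| Schoenfeld, two-sided: 177 events / 0.515 | 344 |
| Two proportions with continuity correction, two-sided | 384 |
| One-sided versions of these four | 280 to 316 |

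The design therefore rests on a two-sided test at 0.05. Every one of these formulas assumes rejection for small P.

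**Step 2. Set the three statements side by side.**

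| Statement | P values that count as significant |
|---|---|
| Sample Size, two-tailed alpha 0.05 | below 0.05 |
| Data Analysis, 95% interval for the hazard ratio excludes 1 | below 0.05 |
| Data Analysis, closing sentence as written | 0.05 and above |

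The number is the same in all three. Only the direction of the third differs. Taken literally, a hazard ratio whose 95% interval excluded 1 would be declared not significant.

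**Step 3. What the literal rule would do.**

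- No true effect: P(P ≥ 0.05) = 1 − 0.05 = **0.95**, against 0.05 as designed.
- Planned effect with 180 per arm: power under the usual rule is 90.1% (two proportions) or 91.4% (Schoenfeld, 360 × 0.515 ≈ 185 events). The literal rule would then declare significance with probability 1 − 0.901 = **0.099** or 1 − 0.914 = **0.086**.

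**Step 4. After the correction.** With P < 0.05, two-sided, alpha is 0.05, power at 180 per arm is 90.1% or 91.4% as above, and N stays at 360. No design figure moves.

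**The case against.** The strongest reply is that nobody would apply the sentence literally. The cut-off agrees across the two sections, and the alpha and the 95% intervals both show that small P values were meant. The phrase can also be heard as *significant at least at the 0.05 level*. On that view the practical effect on error rates and conclusions is nil. This largely stands: the point concerns wording, and the intent is clear. It does not remove the point, because the sentence is complete, wrong as written and corrected nowhere. The charitable reading does not repair it either, since a level at least as strict as 0.05 leaves the actual threshold open. An analysis plan that is not shown might state the rule correctly, but this sentence would still be wrong.

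Three stronger readings are tempting, and the documents do not support them.

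- *That the trial would run with a 95% type I error.* This follows only from literal application, which the alpha and the 95% intervals contradict.
- *That leaving out sidedness in the closing sentence is a second error.* Sample Size gives it as two-tailed for the primary comparison, and 95% intervals match a two-sided 0.05 test. A condensed article need not repeat it.
- *That the sentence formally controls the further analyses, which are made conditional on the primary endpoint being fulfilled.* The article never says that fulfilment is judged by this sentence, and it labels those analyses post hoc.

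**Conclusion.** The point holds as an error of direction in a single sentence. The closing rule of Data Analysis contradicts both the alpha in Sample Size and the confidence level in its own section. It is almost certainly a slip, and its effect on the design is zero: 360 patients, 90% power and alpha 0.05 all stand. Its importance comes from its place. It is the only significance rule stated in the analysis section, and read as written it turns every significant result into a non-significant one and the reverse. The 95% and the 9 to 10% measure that literal reading only. They rest on the planned risks of 60% and 43% with 180 patients per arm and, for the Schoenfeld figure, on proportional hazards. They do not forecast how the trial will be analysed.

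**What to change.** Replace the last sentence of Data Analysis with: *Two-sided P values below 0.05 are considered statistically significant.* This restores agreement with Sample Size and with the 95% intervals, and it gives the secondary and interaction tests a usable rule.

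Nothing further needs to go into that sentence. In particular, it should not also name the treatment term of the Cox model as the primary test. The plan includes interaction terms with response to CRT. If such a term is in the same model, then under usual reference coding the treatment coefficient is the effect in one response group only, so the addition could create a new ambiguity.

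The cost is one sentence. No recalculation and no change to the design, the conduct or the data collected is needed.
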